## Abstract

**Background:**

Schizophrenia spectrum disorders (SSD) are ranked among the leading causes of disabilities worldwide. Many people with SSD spend most of their daily time being inactive, and this is related to the severity of negative symptoms. Here, we present the 3-year DiAPAson project aimed at (1) evaluating the daily time use among patients with SSD living in Residential Facilities (RFs) compared to outpatients with SSD and to the general population (Study 1); (2) evaluating the quality of staff-patient relationships, its association with specific patient outcomes and the quality of care provided in RFs (Study 2); and (3) assessing daily activity patterns in residential patients, outpatients with SSD and healthy controls using real-time methodologies (Study 3).

**Methods:**

Study 1 will include 300 patients with SSD living in RFs and 300 outpatients; data obtained in these clinical populations will be compared with normative data obtained by the National Institute of Statistics (ISTAT) in the national survey on daily time use. Time use assessments will consist of daily diaries asking participants to retrospectively report time spent in different activities.

In Study 2, a series of questionnaires will be administered to 300 residential patients (recruited for Study 1) to evaluate the quality of care and staff-patient relationships, level of well-being and burnout of RFs’ staff, and quality of RFs using a European standardized questionnaire (QuIRC-SA).

In Study 3, the daily time use will be evaluated in a subgroup of 50 residential patients, 50 outpatients and 50 healthy controls using the Experience Sampling Method approach (participants will complete a brief questionnaire -about time use, mood and perceived energy- on a smartphone 8 times a day for 1 week) to compare retrospective and real-time reports. Moreover, their level of physical activity, sleep patterns, and energy expenditure will be monitored through a multi-sensor device.

**Discussion:**

This project is highly innovative because it combines different types of assessments (i.e., retrospective and real-time reports; multi-sensor monitoring) to trace an accurate picture of daily time use and levels of physical activity that will help identify the best therapeutic options promoting daily activities and physical exercise in patients with SSD.

**Trial registration:**

ISRCTN registry ID ISRCTN21141466.

## Background

Schizophrenia is one of the most disabling and severe mental disorders: while its incidence and prevalence are relatively low (McGrath and colleagues found a median prevalence of schizophrenia of 15.2 per 100,000 persons and a median lifetime morbid risk for schizophrenia of 7.2 per 1000 persons), its burden is substantial both for individuals and society [1, 2].

Here, we present the DiAPAson study, a 3-year-long project aimed at fostering our knowledge about the daily time use among people with Schizophrenia Spectrum Disorders (SSD) using different methodologies. The study will address the relationship between the daily time use and negative symptoms and will evaluate the level of Physical Activity (PA), which is known to be reduced in this clinical population. We will also investigate the quality of the staff-patient relationships and the quality of care in Residential Facilities (RFs), which provide long-term care in a country where all former mental hospitals have been shut down.

### Time and psychopathology: historical roots

The study of time and its perception among people with different types of mental disorders has long been an object of investigation for scientists and clinicians active in this field. The idea that temporality had a connection with the state of mind was initially formulated by Augustine of Hippo in his “Confessions” [3]. Later, over the nineteenth century, time became an essential variable for the emerging experimental or natural sciences until the philosopher Henri Bergson recognized the special status of the “subjective” time, in contrast to “objective” or chronological time: he called the former *“lived time”,* characterized by the expansion of vital momentum [4]. The prominent German philosopher Heidegger identified the very meaning of being in the future (as opposed to the past and the present) and thoroughly reflected on the temporality of human existence [5]. However, it was the French (born in Poland) psychiatrist Eugene Minkowski, relying on his Bergsonian readings, to work on the notion of time in psychiatry: in 1914, he published a monograph entitled *“The Essential Elements of Time-Quality*”*,* and in 1933, he produced his fundamental book entitled “Lived Time: Phenomenological and Psychopathological studies”, where he draws a vision of mental disorders based on temporality [6, 7]. Melancholy, in particular, was seen as a disorder where the past was frozen and no longer “passing”: in depression, time does not allow the present and the future to happen; on the contrary, in mania, time runs away, and the patient is unable to stop it. Overall, temporality in psychopathology can be considered the primary modality constituting the experience, that is, it gives shape to the experience, as well as to the symptoms of mental disorders.

### Daily time use in the general population and in people with severe mental disorders

“Daily time use” has been investigated since the late 1920s in the US, initially with a focus on economic productivity and inequalities in labour force and later expanded to assess the use of time among different socioeconomic groups [8]. Within a few years, this research area became of high relevance to describe social conditions and understand people’s behaviour, so that governments in different countries started to map how people used their time with “time use surveys” (TUS [9]). More recently, in 2000, Eurostat released a series of methodological guidelines for facilitating the data collection process and comparison over time of daily time use within and between countries (i.e., Harmonised European Time Use Surveys; HETUS).

Importantly, TUS validation has also allowed a comparison between normative and clinical samples. Several studies have shown that mental disorders are negatively linked to engagement in structured activities throughout the day [10, 11]. While it has long been known that many people with SSD are mainly inactive and apathetic, only recently the study of daily time use has started to be conducted with valid methodologies. These studies have shown that patients with SSD spend significantly less time engaging in structured, functional and social activities and more time resting and “doing nothing” than non-clinical populations [11, 12]. The disorder has a severe impact on social and leisure activities [13], producing a self-maintenance cycle for negative symptoms and influencing functional outcomes [14, 15]. All these findings highlight the importance of assessing daily time use, especially in at-risk populations such as individuals with SSD.

### How to assess daily time use in patients with schizophrenia?

Time-use surveys are usually conducted through semi-structured interviews where participants are asked to retrospectively report the time spent in a variety of daily activities. According to the latest HETUS guidelines, TUS provide comprehensive coverage of all activities in which the subject was involved during the day and facilitate epidemiological research into cross-national comparisons and trend analyses [8].

However, the use of clinical interviews and questionnaires for assessing time use in SSD patients might be biased due to their memory deficits [16, 17], with increased reporting of time engaged in activities while they are indeed “doing nothing” [12]. Thus, recent studies on time use in this clinical population have been based on prospective and real-time assessments, such as the Experience Sampling Method (ESM) approach [18]. The ESM approach provides an ecologically valid time sampling of self-reports that allows studying person-environment interactions in daily time use (e.g., places, people, activities, emotions). Furthermore, it gives instant estimates of current behaviour that are less vulnerable to recall biases [19–22]. This approach might be particularly efficient in evaluating SSD patients given their cognitive deficits and inclination to biases [23]. To assess instantaneous estimates of behaviour, current practice adds real-time measurements taken from accelerometers to ESM data [21, 24]. A recent study demonstrated the feasibility, sensitivity, reliability and validity of ESM methods to assess functioning in patients with SSD [18].

### Physical activity in people with SSD

SSD patients show higher morbidity and mortality compared with the general population [25]. Overall, these patients are at risk for physical comorbidities [26], mainly cardiovascular diseases, metabolic syndromes and diabetes, which cause a 7–20 year reduction in life expectancy [27–31]. Sedentary behaviour and low PA are risk factors for the development of these medical conditions and thus premature mortality [32, 33].

The effect of PA on chronic disease prevention is well documented [34]. In SSD patients, PA interventions have been shown to improve global cognition, working memory and attention [35] and increase white matter connectivity, brain volume, and serum brain-derived neurotrophic factor levels [36, 37]. Moreover, PA shows positive effects on psychological well-being and anxiety [38] and can improve mental and physical quality of life, reducing metabolic risk and overweight [39, 40]. Given that sedentary behaviour is an independent predictor (from PA) of cardiovascular diseases [41], emerging evidence suggests the importance of monitoring both PA and sedentary behaviour in SSD patients [42].

Collecting precise data on the actual levels of PA and sedentary behaviour is, therefore, of paramount importance in SSD patients. In this project, we will use objective measurement methods, such as (i) overall PA dose, assessed as the amount (minutes per day) and intensity (metabolic equivalents) and (ii) amount of sedentary time and sleep quantity and quality.

### Previous Italian studies investigating the time spent doing nothing among SSD patients

In Italy, some studies conducted among a large sample of patients staying in RFs have shown that most patients (in particular patients with SSD) spend little time in meaningful activities and have low levels of PA. In the nationwide PROGRES survey, de Girolamo et al. [43] found that 45% of the sample of 2932 residential patients was inactive, not even assisting with domestic activities in the facility.

Low levels of activity among RFs’ patients have been confirmed by a more recent longitudinal study (PERDOVE study, [44]) conducted among 403 patients hosted by 22 RFs in Northern Italy. This study evaluated in detail the daily time use, showing that (i) 30.8% of the sample spent most of their time alone and uninvolved in any activity; (ii) approximately 1/3 of the patients did “nothing” for more than 6 h/day; and (iii) negative symptoms in patients with SSD were highly prevalent. Similar findings have been obtained in other studies with patients living in RFs [45]. Surprisingly, there are very scant data about the amount of time spent in structured activities among outpatients with SSD, and this makes it impossible to understand whether the amount of daily time spent in meaningful activities is higher, comparable or lower among outpatients with SSD, living independently or with their families, compared to SSD patients living in RFs. Indeed, someone may argue that patients living in the community (often alone) may be more likely to be inactive than patients living in an assisted environment, where staff can stimulate patients and engage them in structured activities.

Given the importance of daily time use and its correlation with psychopathology, it is justified to state that time management represents one of the more informative prognostic indicators for patients with SSD.

### Quality of care and interpersonal relationships in residential facilities

For patients living in RFs, the quality of therapeutic relationships with staff plays a critical role and is a powerful predictor of patient outcomes [46–48]. Bordin [49] provided a useful framework to investigate the quality of the therapeutic relationship by introducing the concept of “working alliance”. The three main components of the therapeutic alliance are agreement on goals, assignment of tasks and development of bonds.

Another fundamental aspect to consider when exploring the quality of relationships in mental health settings is the level of burnout among staff members. An extensive literature has shown how working in mental health settings and experiencing and dealing with patients’ suffering on a daily basis places the clinical staff at risk for burnout [50, 51].

For all these reasons, it is essential to assess the overall quality of care and staff-patient relationships in long-term settings (such as RFs) and correlate these data to the overall functioning of patients living in these facilities.

## Hypotheses and objectives

The assumption underlying the DiAPAson project is that patients with SSD, living in RFs or living independently in the community, spend more time during the day “doing nothing” compared to the general population. We also assume that psychiatric severity, in particular, the severity of negative symptoms, will be positively correlated with the amount of time spent doing nothing.

Additionally, we hypothesize that significant discrepancies will be found comparing the assessment of daily time using a standard paper-and-pencil approach and the ESM methodology. Moreover, we assume that patients with SSD evaluated with real-time assessment through ESM and with appropriate body sensors (actigraphy) will show significant differences when compared to healthy controls: we suggest that specific patterns of associations related to the type of activity performed during the day, the perceived level of energy, PA level and mood will be found.

Finally, we assume that staff well-being and burnout levels will be associated with the quality of staff-patient relationships and specific patient outcomes and that ratings of RF’s quality using the QuIRC-SA will be positively associated with patients’ satisfaction.

### Objectives

The three main aims of the DiAPAson study, a 36-month-long project, are as follows:

#### Objective 1

To evaluate the daily time use (e.g., use of time spent in different activities) of patients with SSD living in RFs compared to outpatients with SSD and to a large, normative sample of the general population; to assess the relationship between the severity of psychiatric symptoms (in particular negative symptoms) and the amount of time spent doing nothing and being sedentary.

#### Objective 2

To assess the quality of staff-patient relationships for patients living in RFs and its relationship with the staff’s well-being and burnout, and to evaluate the quality of RFs rated by service managers using the Quality Indicator for Rehabilitative Care – Supported Accomodation (QuIRC-SA).

#### Objective 3

To compare real-time ESM data about daily activities with retrospective, paper-and-pencil assessments to evaluate the consistency between these two data collection methodologies, and to assess levels of PA with a multi-sensor monitor (actigraphy) in three groups (RF patients and outpatients with SSD compared to healthy subjects).

## Methods/Design

### Study design and management

Data collection will take place in many Departments of Mental Health (DMHs) and RFs across the country, and will start in June 2020; data collection will end on May 2021. The project will be coordinated by the IRCCS Fatebenefratelli of Brescia (coordinating centre), the DMH of Modena and the DMH of Pavia. To date, approximately over 35 DMHs and RFs have expressed written interest for inclusion in the project (see Acknowledgements for a list of participating facilities). Formal agreements are currently being finalized.

Participants will be selected according to the inclusion and exclusion criteria shown in Table 1. They will approve and sign an informed consent form before inclusion in the study. The flow diagram shown in Fig. 1 provides a clear picture of enrolment and assessment procedures of all study subjects.

**Table 1 Tab1:** Patients’ recruitment: inclusion and exclusion criteria

	Inclusion criteria	Exclusion criteria
All groups	- Age 20–55 years old; - Good knowledge of Italian language.	- Inability to provide informed consent (because of low education, or cognitive impairment); - Severe cognitive deficit (MMSE equal or lower than 24.0); - Lifetime diagnosis of substance use disorder according to DSM-5 criteria (APA, 2013 [52]); - History of clinically significant head injury; - Cerebrovascular, neurological disease.
G1 and G2	- SSD diagnosis according to DSM-5 (APA, 2013 [52]); - In charge to a RF or to a DMH as outpatient.

**Fig. 1 Fig1:**
[figure not shown]
Flow-diagram showing procedures for enrolment and assessment of clinical subjects and healthy controls

### Study 1 design

#### Participants

The sample will include 300 residential patients diagnosed with SSD (G1), matched by age and gender to 300 outpatients (G2). General population data will be extracted from the National Institute of Statistics (ISTAT) survey “*Uso del tempo quotidiano*”, a national survey that assesses how people spend their time, which was conducted in 2013 in Italy (ISTAT, https://www4.istat.it/it/prodotti/microdati#file_ricerca) in a representative sample of the Italian population including approximately 27,000 families (with a total of approximately 60,000 surveyed individuals) living in 508 municipalities (out of over 8000 Italian municipalities) of different sizes.

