#### Measures and variables

A general assessment, together with demographics, will include measures of psychiatric symptoms (in particular negative symptoms), psychosocial functioning and time perception. Variables related to daily time use will include the number of daily hours spent in different activities: paid work, study, travel, doing nothing/resting, social/leisure activities, activities related to child/household care, voluntary activities, sport, and hobbies. Table 2 shows a comprehensive overview of the measures and areas of investigation; all reported instruments have been tested for validity and reliability in Italian: Table 2 shows the reference of the original paper for each instrument, and the reference of the Italian validation study. Time use assessments will consist of a pre-filled daily diary (to be completed twice a week, on a working day and on a weekend day) adapted from the ISTAT’s national survey on time use, asking participants to retrospectively report the daily time spent in different activities. The time spent in each activity will be calculated as number of hours per week.

**Table 2 Tab2:** Assessment measures, domains and subjects receiving the assessment

Instrument/Reference (original and Italian validation)	Domain	Study group			
		Residential patients	Outpatients	Healthy controls	Staff
Mini Mental State Examination (MMSE) (Cockrell & Folstein, 2002 [53]; Measso et al., 1993 [54])	Cognitive functioning	X	X	X	
Brief Psychiatric Rating Scale (BPRS) (Overall and Gorham, 1962 [55]; Morosini et al., 1995 [56])	Psychiatric functioning	X	X		
Brief Negative Symptom Scale (BNSS) (Strauss et al. 2012 [57]; Mucci et al., 2015 [58])	Negative symptoms	X	X		
Specific Levels of Functioning Scale (SLOF) (Schneider et al., 1983 [59]; Mucci et al. 2014 [60])	Current functioning and behaviour	X	X		
World Health Organization Quality of Life Brief version (WHOQOL-Bref) (Whoqol Group, 1998 [61]; de Girolamo et al., 2000 [62])	Quality of life	X	X		
World Health Organization Disability Assessment Schedule 2.0 (WHODAS 2.0) (Gold, 2014 [63]; Federici et al., 2009 [64])	Psychosocial functioning	X	X		
Zimbardo Time Perspective (ZTPI-short form) (Zimbardo & Boyd, 2015 [65]; Laghi et al., 2009 [66])	Attitude towards time	X	X	X	
Positivity Scale (P Scale) (Caprara et al., 2012 [67])	Positivity assessment	X	X		
Time Use Survey (TUS) (see HETUS, 2019 [68])	Use of daily time	X	X	X	

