### Study 3 design

#### Participants

The sample will include a sub-group of at least 50 RF patients (drawn from G1), 50 outpatients (drawn from G2) and 50 healthy controls from the general population matched by age and gender. This latter group will also complete the TUS. Healthy controls will be recruited through ads, both using the project’s website and spreading the news of the study through social networks.

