### Data analyses

#### Study 1

Data on daily time use in the different groups will be compared using parametric and non-parametric methods depending on the distribution of the investigated variables. Correlation estimates (Pearson or Spearman) will be used to assess the associations between the severity of psychiatric symptoms and the amount of sedentary time.

Sample size was calculated based on Cella and colleagues’ study [12], which compared patients with SSD (*N* = 170) and a general population sample (*N* = 1124). Their results showed that the average time spent “doing nothing” (target) in the patient group was 5.17 h per day, while for the general population, it was 0.76 h with a standard deviation of 5 for both groups. With such data, the effect size for a linear model is 0.44. As a precaution, assuming a lower effect size equal to approximately 0.15, using ANCOVA (including age and gender in the model) with three groups, and choosing a power of 0.8, the estimated total sample size is equal to *N* = 435. Moreover, considering a total of approximately 25 different recruitment centres, the correction for the design effect (DE = 1 + (435/25–1)*0.02 = 1.3, with an intraclass correlation coefficient equal to 0.02) leads to a sample size of about *N* = 570, which was increased to *N* = 600 (300 for each group) to account for possible dropouts of about 10%. Finally, 300 matched subjects randomly sampled from the ISTAT general population sample will be added as third group, for a total of *N* = 900 subjects evaluated for daily time use.

#### Study 2

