### Study status

The current protocol is updated to February 2020. Recruitment will take place from June 2020 to July 2021.

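### In Study 1's patient-versus-population contrast, calendar period and diary version coincide with patient status; the concurrent controls' diaries should be added as a sensitivity analysis

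*Protocol article*

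**What the plan says.** Under Study 1 design, Participants, the general population data come from the ISTAT daily time-use survey, "which was conducted in 2013 in Italy", a representative sample of roughly 60,000 people. The Data analyses section fixes how it enters: "300 matched subjects randomly sampled from the ISTAT general population sample will be added as third group", giving 900 subjects in all. The sample size model there is a three-group ANCOVA with age and gender as covariates.

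Patients are seen much later. Study design and management says that data collection "will start in June 2020; data collection will end on May 2021"; Study status says "Recruitment will take place from June 2020 to July 2021". The two end dates differ, but both put the patients seven to eight years after the survey. Under Study 1, Measures and variables, the patient instrument is a pre-filled diary for one working day and one weekend day, "adapted from the ISTAT’s national survey on time use". The Study 1 Procedure adds a 20-minute training session on the diary.

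Study 3 recruits "50 healthy controls from the general population matched by age and gender" and adds: "This latter group will also complete the TUS". Table 2 confirms that healthy controls receive the time-use survey. The only analysis stated for retrospective reports under Study 3 is their agreement with the smartphone reports.

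**The concern.** That patients spend more time doing nothing than the general population is the project's first hypothesis and part of Objective 1. As the comparison is built, three things change together between the patient and population groups: illness, calendar period, and the version of the diary (with its training). No record in the three-group model breaks that pattern, so no covariate can separate them. Matching or adjusting for age and gender deals with those two variables and nothing else.

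Any change in population time use after 2013, and any effect of the adapted form, would enter the estimated patient-population difference in full. The Limitations section discusses assessment burden and the non-random choice of facilities, but not this. Meanwhile the design already collects diaries from people without the illness, in the same period and with the study's own time-use survey, and states no Study 1 use for them.

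**Working it through.** **Inputs.** All from Data analyses, Study 1, unless noted: mean time doing nothing 5.17 h/day in patients and 0.76 h/day in the population, SD 5; planning effect size 0.15; power 0.8; ICC 0.02; about 25 centres; about 10% dropout; groups of 300, 300 and 300. Fifty concurrent controls (Study 3, Participants). Two-sided alpha of 0.05 is assumed because the article states none.

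**1. The plan's own figures.**
- Difference: 5.17 − 0.76 = 4.41 h/day; 4.41/5 = 0.88 SD; half of that is 0.44, the stated effect size.
- Three-group ANCOVA with f = 0.15 and power 0.8, by the noncentral F distribution: N = 432, against 435 stated.
- Design effect: 1 + (435/25 − 1) × 0.02 = 1.328; 435 × 1.328 = 578, or 566 with the factor rounded to 1.3, against about 570 stated.

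The inputs are therefore read as the plan intends, and the point below does not dispute these three figures.

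**2. Who carries which attribute.**

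| Group | Period | Diary | Patient | In the Study 1 model |
|---|---|---|---|---|
| Residential, outpatients | 2020-21 | adapted | yes | yes |
| ISTAT respondents | 2013 | ISTAT's own | no | yes |
| Concurrent controls | 2020-21 | study TUS | no | not stated |

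Within the Study 1 model, period and diary are fixed by patient status. The stated total of 900 is 300 + 300 + 300, which leaves no place for the controls. The two patient groups share period and diary, so the contrast between them is clean in this respect, as are the symptom correlations within patients.

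**3. What shift would matter.** The document gives no figure for a shift, so these sizes are assumptions.
- The planning effect in hours: 2 × 0.15 × 5 = 1.5 h/day for two groups. For three groups with equal patient means it is 0.15 × 5/√(2/9) = 1.59 h/day.
- SE for 300 versus 300: 5 × √(2/300) = 0.41 h/day. With no illness effect at all, the chance of a significant difference is:

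| Assumed shift (h/day) | No design effect | Design effect 1.3 on patients |
|---|---|---|
| 0.25 | 0.09 | 0.09 |
| 0.5 | 0.23 | 0.21 |
| 1.0 | 0.69 | 0.63 |
| 1.5 | 0.96 | 0.93 |

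- The expected 4.41 h/day is 4.41/1.5 = 2.9 times the two-group planning effect.

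**4. What 50 controls can show.**
- Against one patient group after 10% dropout (270): SE = √(1/50 + 1/270) = 0.154 SD. Detectable at 80% power: 2.80 × 0.154 = 0.43 SD; against all 540 patients, 0.41 SD.
- At the expected 0.88 SD: 0.88/0.154 = 5.7 standard errors, power above 99%.
- At the planning effect of 1.5/5 = 0.30 SD: 0.30/0.154 = 1.95 standard errors, power about 50%. With 300 patients and 1.59 h/day, power is about 55%.
- Controls minus ISTAT (50 versus 300): SE = 5 × √(1/50 + 1/300) = 0.76 h/day; 95% half-width 1.96 × 0.76 = 1.5 h/day.

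**The case against.** The comparator is a deliberate and reasonable choice. ISTAT is large and representative, the patient diary derives from that same survey, and the Background presents harmonised time-use methods as allowing normative and clinical samples to be compared. The article does not say how far the adapted form departs from ISTAT's, nor what training ISTAT respondents had, so an instrument effect is a possibility of unknown size. All of this stands. It is a reason to keep ISTAT as the main comparator, but a common origin does not make the forms identical, and representativeness for 2013 does not address period.

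A second objection is that a sensitivity contrast belongs in the full protocol or analysis plan, and that the general statement about comparing groups does not exclude the controls. This stands in part. The article does, however, fix the comparator, the number of groups and the total, and the point concerns that choice rather than a missing detail.

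Third, Study 3 gives concurrent evidence on inactivity with the same instruments in all three groups: the smartphone reports include resting or doing nothing, and the actigraph measures idle time. A reader might infer that the project has no concurrent same-instrument evidence at all, or that the controls' diaries go unused. Neither is so. The gap is confined to the Study 1 diary contrast.

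Fourth, the remedy is imperfect. The controls are volunteers recruited through the project's website and social networks, and Table 1 applies its exclusions to all groups; no such screening is described for ISTAT respondents. Controls versus ISTAT would therefore mix selection with period and instrument. This stands and limits how that contrast may be labelled.

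**Conclusion.** The confounding of period and diary version with patient status is real and follows from the design as stated. It affects only the patient-versus-population contrast. Its size cannot be known from the document.

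A reader might go further and infer that the headline result would be an artefact, or that no population claim can be made without a concurrent reference. The document does not support that. It gives no figure for any change since 2013, and a shift would have to approach 4.41 h/day to produce the expected result by itself. The direction for time doing nothing would probably survive a moderate shift. Differences nearer the planning effect, about 1.5 h/day, are more exposed, and the other activity categories may be too.

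Nor do the figures support making the population claim conditional on agreement with the controls. At 0.30 SD such a check has about 50% power, and disagreement could reflect volunteer selection alone. The numbers assume SD 5, two-sided alpha 0.05 and, for the control contrasts, no design effect. With 1.3 applied to 300 patients, the SE rises only from 0.76 to 5 × √(1/50 + 1.3/300) = 0.78 h/day.

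**What to change.** Keep the matched ISTAT sample as the main population comparator. Add to the Study 1 analysis, as a pre-specified sensitivity analysis, each patient group versus the 50 concurrent healthy controls on time-use survey hours, adjusted for age and gender, with confidence intervals reported beside the ISTAT contrast.

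Optionally, report controls versus age- and gender-standardised ISTAT respondents. Label it a descriptive shift that combines period, instrument and volunteer or screening selection, with an expected 95% half-width of about 1.5 h/day at SD 5.

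Do not make the population claim formally conditional on either result; interpret any disagreement as a limitation. Add a sentence to the Limitations naming the 2013 survey date and the adapted diary.

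The cost is analysis wording and a little reporting space, since the control diaries are already planned. The drawback is that the controls are few and self-selected, so they check the ISTAT contrast and cannot replace it.
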